### Definitions

#### Depression/Presence of Depressive Symptoms

The diagnosis of MDD is based on the mini-international neuropsychiatric interview (MINI). A score of ≥15 on the MADRS is also used to diagnose MDD.

#### Anxiety/Presence of Anxiety Symptoms

The diagnosis of GAD is based on MINI. A score of ≥8 on the GAD-7 is also used to diagnose GAD.

#### Treatment Success

Treatment success is defined as a reduction in the MADRS/GAD-7 scores by 50% from the baseline. Those who do not meet the 50% threshold are considered nonresponders. Nonresponders at the week 4 visit will be given a booster dose.

#### Treatment Failure

Treatment failure is defined as same or increased MADRS/GAD-7 scores from pre- to post-treatment.

### Study Setting

This study is being carried out at the Providence Care Hospital, a tertiary care mental health and continuing care hospital in Kingston, Ontario There will be a total of 7 visits, of which 6 will be in-person and 1 will be over the phone.

### Participants

A total of 10 to 15 eligible participants aged between 18 and 65 years will be recruited from the Kingston area. At the first visit, consent will be obtained from potential trial participants by a study team member and overseen by the principal investigator. Following informed consent, the participants will be screened to ensure that they fit the inclusion criteria (Textbox 1). In this study, we define depression as a confirmed diagnosis of MDD based on the MINI and a score of ≥15 on MADRS; anxiety is defined as a confirmed diagnosis of GAD based on the MINI and a score of ≥8 on the GAD-7. These participants are not to be in a current episode of MDD or GAD and should not have been taking any antidepressant medication. Textboxes 1 and 2 provide the full study criteria. 

Inclusion criteria.Able to provide informed consentNot pregnantWilling to participate in follow-up as part of the studyDiagnosis of major depressive disorder and/or generalized anxiety disorder (GAD) by the mini-international neuropsychiatric interviewCurrent depressive episode with a Montgomery-Asberg depression rating scale score of ≥15 or current GAD episode with a GAD 7-item scale score of ≥8Able to understand and comply with the requirements of the studyAble to provide stool and blood samples

Exclusion criteria.History of chronic diarrheaNeed for regular use of agents that affect gastrointestinal motility (narcotics such as codeine or morphine and agents such as loperamide or metoclopramide)ColostomyElective surgery that will require preoperative antibiotics planned within 6 months of enrollmentPregnant, breastfeeding, or planning to get pregnant in the next 6 monthsAny condition for which, in the opinion of the investigator, the participant should be excluded from the studyCurrent use of any antidepressant/antianxiety drug (eligible to participate after a 4-week washout period)Use of any antibiotic drug in the past 4 weeks (may be eligible to participate after a 4-week washout period)History of alcohol or substance dependence in the past 6 monthsDaily use of probiotic products in the past 2 weeks (may be eligible to participate after a 2-week washout period)Use of any type of laxative in the last 2 weeksConsumption of products fortified in probiotics

### Recruitment

Participants were recruited from the Kingston community using web-based and paper advertisements. Web-based advertisements were posted on the internet to social media platforms such as Facebook and Twitter. Posters were posted around Kingston—on university and college campuses, community bulletin boards, clinics, and counsellor centers. Recruitment was completed in December 2019.

### Treatment Compliance

Treatment compliance was assessed by recording unused clinical trial material and reviewing participants’ personal logs.

### Discontinuation Criteria

A participant may be discontinued from treatment or withdrawn from the study at any time if the participant, the principal investigator, or the investigational product sponsor does not feel that it is not in the participant’s best interest to continue. The following is a list of possible reasons for treatment discontinuation:

Participant’s withdrawal of consentAn AE that in the opinion of the investigator would be in the best interest of the participant to discontinue the study treatmentProtocol violation requiring discontinuation of the study treatmentLost to follow-upRequest by NuBiyota LLC for early termination of the studyNewly pregnant participants.

If a participant is withdrawn from treatment due to an AE, the participant will be followed up and treated by the investigator until the abnormal parameter or symptom has resolved or stabilized. All participants are free to withdraw from participation at any time, for any reason, specified or unspecified, and without prejudice. Reasonable attempts will be made by the investigator to provide a reason for the withdrawal of participants. No further data will be collected once a participant has been withdrawn.

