### Statistical Analyses

Treatment success and failure will be measured individually. Those who have an improvement of at least 50% in MADRS or GAD-7 scores will be considered responders. The SPSS will be used to analyze all data from clinical measures obtained throughout the study. Repeated measures analysis of variance (ANOVA) will be used to analyze changes in clinical measures from baseline to week 10. Paired *t* tests will be used to compare clinical measure means at each time point with the baseline. If a participant returns after the first course of treatment and is later withdrawn, their final scores for primary outcomes will be projected to week 10. In the event of missing data, the data from the last time point will be projected forward. Similarly, stool samples will be analyzed to provide diversity scores, which will then be compared using paired *t* tests and repeated measures ANOVA. Changes in diversity scores will be compared with clinical scores to assess for correlations.

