### Adverse Events

The frequencies and severity of AEs will be collected on a questionnaire from the first day of the assigned study treatment through 14 days following the last assigned study treatment. AEs will be assessed and recorded at all in-hospital visits and phone calls; they will be categorized by frequency, severity, and causality.

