#### Causality

To gauge the causal relationship of the AEs to the treatment, the following 4-point scale will be used:

Probable (4 points): A clear-cut temporal association with improvement on cessation of investigational medicinal products or reduction in dose. Reappears upon rechallenge.Possible (3 points): Follows a reasonable temporal sequence from administration. May have been produced by the subject’s clinical state, environmental factors, or other therapies administered.Unlikely (2 points): Does not follow a reasonable temporal sequence from administration. May have been produced by environmental factors or other therapies administered.Unrelated (1 point): Due only to extraneous causes and does not meet the criteria listed under unlikely, possible, or probable.

The investigator will probe, via discussion with the participant, for the occurrence of AEs during each patient visit and record the information in the site’s source documents. AEs will be recorded in the participant case report form. AEs will be described by duration (start and stop dates and times), severity, outcome, treatment, and relation to the study drug or, if unrelated, the cause.

AEs will be collected in the following ways: (1)any symptoms or events self-reported spontaneously by the patient,

(2) the patient will be asked open-ended questions to answer about their health (eg, “How are you feeling since we saw you last in clinic?”), and (3) any clinically relevant abnormalities noted by the investigator during follow-up interviews.

In the event of a reported AE, if the principal investigator decides that it would be in the best interest of the participant to discontinue treatment, the participant will be removed from the study. If a participant is withdrawn from treatment due to an AE, the participant will be followed and treated by the investigator until the abnormal parameter or symptom has resolved or stabilized.

Once withdrawn, if participants choose to withdraw the biological samples they provided before the AE, they are able to do so, and we will ensure that the samples are destroyed. If tests have already been performed on the sample(s), it will not be possible to withdraw those results. However, no further testing will be performed. The samples that have already been tested will continue to the analysis portion of the study. 

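### For treatment stops caused by an adverse event, the removal rule and the no-further-data rule contradict the adverse-event follow-up, and later MADRS and GAD-7 scores are replaced by carried-forward values.

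*Protocol article*

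**What the plan says.** The Discontinuation Criteria open by naming two events: "A participant may be discontinued from treatment or withdrawn from the study at any time". One list of reasons for stopping treatment follows, and it includes withdrawal of consent and loss to follow-up, which are exits from the study. For a participant taken off treatment because of an AE, the section says that "the participant will be followed up and treated by the investigator until the abnormal parameter or symptom has resolved or stabilized". It closes with: "No further data will be collected once a participant has been withdrawn".

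The Causality subsection under Adverse Events covers the case where the principal investigator judges, after a reported AE, that it is best "to discontinue treatment, the participant will be removed from the study". It then repeats the follow-up to resolution. It also asks for each AE to be described by, among other items, its stop date and outcome.

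The Safety and Tolerability and Adverse Events sections collect AEs "from the first day of the assigned study treatment through 14 days following the last assigned study treatment". Neither makes an exception for withdrawn participants.

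The Statistical Analyses section says that, for a participant who returned after the first course and was later withdrawn, "their final scores for primary outcomes will be projected to week 10". More generally: "In the event of missing data, the data from the last time point will be projected forward".

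**The concern.** Site staff handling an AE-driven stop have rules that point in opposite directions: stop collecting data, keep collecting all AEs for 14 days, and follow the event to its end. Different staff could apply different rules, and the data would not show which was used.

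Safety and tolerability are stated aims of this phase 1 trial. If the data-stop rule wins, the participants who tolerated the product worst have the shortest AE observation, and an event still open at removal may have no recorded stop date or outcome. The same participants lose their later primary-outcome scores because of a study rule and not by their own choice. With a planned 10 to 15 participants, each such loss carries weight.

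**Working it through.** The article gives no figure for this point, so the check compares the rules and then counts what the schedule loses.

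**Step 1: does an AE stop trigger the data stop?** The Causality subsection turns an AE-driven treatment stop into removal from the study. Its later paragraph on stored samples uses the word *withdrawn* for these same participants. The last sentence of the Discontinuation Criteria ends data collection once a participant is withdrawn. Read together, an AE-driven stop ends data collection.

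**Step 2: which rules conflict with that?**
- The 14-day AE window applies to everyone as written.
- The follow-up to resolution or stabilization appears both in the Discontinuation Criteria and under Causality.
- A stop date and outcome cannot be recorded for an AE still ongoing when collection ends.

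**Step 3: what is lost on the schedule?** Table 2 places MADRS and GAD-7 after baseline at weeks 2, 4, 6, 8 and 10, which is 5 scores each. For a stop at visit week s, after that visit's scores are taken:
- unobserved scores = number of scheduled weeks later than s
- span bridged by carrying forward = 10 − s weeks
- end of the 14-day window, counted from the stop = week s + 2

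| Stop at | Unobserved visits | Share of 5 | Span carried | AE window ends |
|---|---|---|---|---|
| Week 2 | 4, 6, 8, 10 | 4/5 = 80% | 8 weeks | Week 4 |
| Week 4 | 6, 8, 10 | 3/5 = 60% | 6 weeks | Week 6 |
| Week 6 | 8, 10 | 2/5 = 40% | 4 weeks | Week 8 |

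In each row the data-stop rule, applied literally, removes the whole 14-day window.

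**Step 4: what replaces the scores?** The Statistical Analyses section carries the last value forward. After a week 2 stop, the week 2 score stands as the week 10 primary outcome. If scores would have kept improving, the carried value understates improvement. If an early improvement would have faded, it overstates it. The article gives nothing that decides between the two.

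**The case against.** The best defence is that the no-further-data sentence directly follows two sentences on participants' freedom to leave and the reasons for leaving. It may therefore concern only people who leave the study, while AE stops fall under the follow-up to resolution. This stands in part: the article does not order a clean end to all data after an AE stop, and the fault is a contradiction, not an established loss of safety data. But the reading does not resolve it. The Causality subsection explicitly removes AE stops from the study. Follow-up to resolution concerns the event that led to the stop, so it secures neither new AEs within the 14 days nor the later scales.

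Four stronger readings are tempting, and the article does not support them.

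- A reader might infer that every treatment stop means removal. That is explicit only for AE-driven stops. For other reasons the two events are named separately, without saying what follows.
- A reader might infer that no AE can ever be graded *probable*, because that grade asks for "improvement on cessation of investigational medicinal products or reduction in dose. Reappears upon rechallenge". But it accepts a dose reduction, and Table 1 schedules a fall from 10 to 3 capsules per day and a return to 10 at week 2 (for nonresponders also at week 4). Participants who continue can show the pattern. At most, reappearance on rechallenge cannot be observed after someone has been removed for an AE. Expedited reporting is little affected, since *possible* triggers it as well.
- A reader might take the Results section's 21 enrolled and 12 completers as the size of the problem. No reasons are given for the other 9, and the wording does not establish that they had no post-baseline visit.
- A reader might conclude that the outcomes are biased. The article supports a risk only.

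**Conclusion.** The concern holds for AE-driven stops. The removal rule and the data-stop sentence conflict with the 14-day AE window and with the follow-up to resolution, and the passages must be reconciled. The consequence for the primary outcome is that later scores are unobserved and carried forward: 4 of 5 after a week 2 stop, 3 of 5 after week 4, 2 of 5 after week 6. These counts assume that the stop falls at the visit once its scores have been taken and that the data-stop sentence is applied literally. The article reports no number of AE stops, so the overall effect on the trial cannot be sized. The point deserves correction, but in an uncontrolled, open-label phase 1 study that already lists its small size and lack of placebo as limitations, it does not by itself undermine the design.

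**What to change.** Reconcile Discontinuation Criteria, Safety and Tolerability, Adverse Events and Causality by defining two states: stopped study product, and withdrew consent. End data collection only on withdrawal of consent. For participants who stopped product but still consent, continue AE collection through the stated 14-day window and the already scheduled MADRS and GAD-7 through week 10. This concerns data collection only. When product is stopped and how events are managed stay with the investigator, and the causality scale needs no change on this account.

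The cost is a wording change, notified as the Approvals and Registration section already provides, and a few extra contacts for each stopped participant. One of the 7 planned visits is already by phone.

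Recruitment ended in December 2019 and the data were already being analyzed when the article was written, so unobserved scores probably cannot be recovered. For participants already stopped:
- enter AE outcomes and stop dates from source documents where they exist;
- state which rule was applied in practice;
- report how many week 10 MADRS and GAD-7 values were carried forward after a stop, and from which visit.

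That part costs a record review.

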### Outcome Measures

#### Clinical Measures

Mood, anxiety, and GI symptoms and sleep quality will be assessed at all treatment visits. At week 10, only the MADRS and GAD-7 will be administered. The primary outcome measure will be mood and anxiety symptoms measured biweekly by changes in the MADRS and GAD-7 scores, respectively. The clinical measures include self-rated and clinician-rated measures. The self-rated questionnaires that will be used are the GAD-7 to assess anxiety symptoms and severity, the Snaith-Hamilton pleasure scale to assess anhedonia, quick inventory of depressive symptomatology to assess depressive symptoms, the gastrointestinal symptom rating Scale (GSRS) to assess GI symptoms, the Toronto side effects scale (TSES) to assess tolerability of the therapeutic product, and the Pittsburgh sleep quality index to assess subjective sleep quality. The clinician-rated questionnaires and interviews are the MADRS to assess depressive symptoms and severity, the clinical global impressions scale to assess illness severity and improvement, and the childhood experience of care and abuse questionnaire to assess early life stress and environmental risk factors associated with upbringing. Table 2 gives more details on the scales used in assessing outcome measures.

**Table 2 table2:** Study visit schedule.

Procedure		Screening	Week 0	Week 2	Week 4	Week 6	Week 8	Week 10
**Clinical**								
	ICF^a^ review and signing	X^b^	—^c^	—	—	—	—	—
	Study criteria review	X	—	—	—	—	—	—
	Mini-international neuropsychiatric interview	X	—	—	—	—	—	—
	Demographics	X	—	—	—	—	—	—
	Medical and antidepressant history	X	—	—	—	—	—	—
	Physical examination	—	X	—	—	—	—	—
	Pregnancy test (females)	—	X	—	—	—	—	—
	Montgomery-Asberg depression rating scale	X	X	X	X	X	X	X
	Generalized anxiety disorder 7-item scale	X	X	X	X	X	X	X
	Clinical global impressions scale	—	X	X	X	X	X	—
	Snaith-Hamilton pleasure scale	—	X	X	X	X	X	—
	Quick inventory of depressive symptomatology	—	X	X	X	X	X	—
	Pittsburgh sleep quality index	—	X	X	X	X	X	—
	Toronto side effects scale	—	X	X	X	X	X	—
	Gastrointestinal symptom rating scale	—	X	X	X	X	X	—
	Childhood experience of care and abuse	—	—	—	—	X	—	—
	Adverse events	—	X	X	X	X	X	X
**Molecular**								
	Blood samples	X	—	—	X	—	X	—
	Fecal samples	—	X	X	X	—	X	X

^a^ICF: Informed Consent Form.

^b^X: will be completed.

^c^Will not be completed.

#### Safety and Tolerability

Participants will use a personal mood and symptom log to track any symptoms that they have been newly experiencing since the beginning of treatment, assess the tolerability of treatment, and keep track of their mood and sleep. AEs will be assessed and recorded at all in-hospital visits and on phone calls; they will be categorized by frequency, severity, and causality. The frequencies and severity of AEs will be collected on a questionnaire from the first day of the assigned study treatment through 14 days following the last assigned study treatment. Investigational product safety will be assessed via recorded symptoms and AEs. Investigational product tolerability will also be assessed using the TSES and GSRS during all visits except screening.

### Molecular Analysis

Blood samples will be taken at screening, *w*eek 4, and *w*eek 8 and sent to Core Laboratories at Kingston Health Sciences Centre, Kingston General Hospital to analyze changes in cortisol levels, liver function, lipids, inflammatory markers (cytokines IL-10 and IL-6, TNF-α, TGF-β, and C-reactive protein), neurotransmitters (5-HT, *DA*, and *NE*), and immunoglobulins (IgA, IgG, and IgM). Baseline levels of creatinine, electrolytes, thyroid-stimulating hormone, complete blood count, and glucose will be taken only at screening to ensure that it is safe for participants to consume the investigational product at baseline. Fecal samples will be collected at all in-hospital visits. The participants will be provided with a stool kit and a Styrofoam case, with instructions at each visit. Upon collecting the sample from the participants, it will be stored at –62°C. Throughout the study, the samples will be sent to the University of Guelph for 16s RNA gene sequencing to determine the gut microbiome composition before, during, and after treatment.

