**Methods:**

Adults experiencing depressive or anxiety symptoms will be recruited from the Kingston area. These participants will orally consume an encapsulated MET-2 once daily—containing 40 strains of purified and laboratory-grown bacteria from a single healthy donor—for 8 weeks, followed by a 2-week treatment-free follow-up period. Participants will undergo a series of clinical assessments measuring mood, anxiety, and GI symptoms using validated clinical scales and questionnaires. Molecular data will be collected from blood and fecal samples to assess metabolic changes, neurotransmitter levels, inflammatory markers, and the level of engraftment of the fecal samples that may predict outcomes in depression or anxiety.

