### Gut Microbiome and Psychiatric Symptoms

MDD pathophysiology involves three different physiological systems: (1) neurotransmitter dysfunction between the prefrontal cortex regions in the CNS and the hypothalamic-pituitary-adrenal (HPA) axis, (2) chronic inflammation of the immune system, and (3) an imbalance in the microbiota-gut**-**brain axis [16-20]. The prefrontal cortex, hippocampus, and amygdala play a vital role in the regulation of emotion, anxiety, stress responses, self-control, motivation, and cognitive reactions. However, in depressed patients, the function of the prefrontal cortex and hippocampus is impaired, whereas the activity of the amygdala is increased [21]. These arguments are supported by the monoaminergic neurotransmitter deficiency hypothesis, which postulates that monoamine neurotransmitters serotonin (5-HT), norepinephrine (NE), and dopamine (DA) are at insufficient levels and ultimately result in depressive symptoms. The immune system plays an important role in depression; the cytokine and neuroinflammation hypotheses suggest an increase in pro-inflammatory cytokines (interleukin 6 [IL-6] and tumor necrosis factor alpha [TNF-α]), and a decrease in anti-inflammatory cytokines (interleukin 10 [IL-10] and transforming growth factor beta [TGF-β]), contribute to a pro-inflammatory state in depressed patients. These cytokines inhibit the negative feedback of the HPA axis, increase the permeability of the blood-brain barrier, reduce the synthesis of 5-HT, disturb the glutamatergic systems, and influence neuroglial cells. These actions play a vital role in the regulation of neuro-immunity and neuroplasticity and are hypothesized to result in depressive behavior [22-27]. In 2012, Maes et al [28] showed that bacterial translocation from the gut, or *leaky gut*, which may be due to systemic inflammation in depression or may be a primary trigger that is associated with the onset of depression, can activate immune cells to elicit selective immunoglobulin A (IgA) and immunoglobulin M (IgM) response—both antibodies that fight and protect against infections. The results of this study suggest that this phenomenon may be involved in the pathophysiology of depression by causing progressive amplifications of immune pathways [28].

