#### Secondary Objectives

The secondary objectives are to assess changes in metabolic functioning/levels before, during, and after treatment; to assess safety and tolerability, including adverse events (AEs) with a severity of grade 2 or above; and to assess potential correlation between early life stress (childhood emotional/physical/sexual abuse history, etc) and changes in MDD biomarkers as well as response to treatment.

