## Methods

### Study Design

This is an 8-week, open-label, phase 1 clinical trial assessing the safety, tolerability, and efficacy of MET-2 on depression and anxiety symptoms. All participants will consume the investigational product, MET-2, in *a* capsule form, daily for 8 weeks. MET-2 is administered orally at 0.5 g of MET-2 per capsule, containing 3.2 ×10^5^-3.2×10^11^ colony-forming units (CFUs). At each in-hospital visit, participants take home the appropriate number of MET-2 capsules needed for a 2-week period, packaged in bottles. Loading/booster doses are provided in separate vials from maintenance daily doses. Each vial is stored by the participant at room temperature. MET-2 is meant to be taken after a light meal, preferably in the morning and at the same time every day.

Participants will consume an initial loading dose of 5 g MET-2. An initial MET-2 dose in the range of 10^8^ to 10^12^ CFUs was selected with the aim of ensuring delivery of a sufficient quantity of the MET-2 bacterial community that is expected to colonize the gut. The first loading dose, at baseline, is to be consumed under the supervision of the study staff to ensure immediate safety, and further compliance is assessed using the returned investigational product and by reviewing participants’ personal logs at each in-hospital visit. For the remainder of the 2-week period, the participants will consume 1.5 g of MET-2 per day. The loading dose is repeated for the first 2 days at the week 2 time point, and participants return to the maintenance dose for the remainder of the treatment period. At week 4, participants are assessed for treatment response. Responders remain on the maintenance dose until the end of treatment. Nonresponders are given an additional loading dose (booster dose; Table 1).

**Table 1 table1:** Dosing schedule.

Dose	Baseline to week 2	Weeks 2*-*4	Weeks 4*-*6	Weeks 6*-*8
Loading/booster dose (5 g of MET-2^a^: 10 capsules per day for 2 days)	Days 1 and 2 only	Days 1 and 2 only	Days 1 and 2 (only NR^b^)	N/A^c^
Maintenance dose (1.5 g of MET-2: 3 capsules per day)	Days 3-14	Days 3-14	R^d^: Days 1-14; NR: Days 3-14	Days 1-14

^a^MET-2: microbial ecosystem therapeutic-2.

^b^NR: nonresponders.

^c^N/A: not applicable.

^d^R: responders.

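### Blood count, creatinine, electrolytes, glucose and TSH are scheduled only at screening, so a phase 1 trial with safety among its aims plans no on-treatment value for them, although it redraws blood at weeks 4 and 8

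*Protocol article*

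**What the plan says.** All references are to the protocol article.

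- **Molecular Analysis** fixes the timing of five tests: "Baseline levels of creatinine, electrolytes, thyroid-stimulating hormone, complete blood count, and glucose will be taken only at screening". It gives the purpose as "to ensure that it is safe for participants to consume the investigational product at baseline", that is, a check before the first dose.
- The same section states the timing of the draws: "Blood samples will be taken at screening", then at weeks 4 and 8. They serve "to analyze changes in cortisol levels, liver function, lipids, inflammatory markers", together with neurotransmitters and immunoglobulins.
- **Table 2** agrees on the draws (screening, week 4, week 8, none at week 10). It has one row for blood samples and names no analytes.
- **Study Design** describes the trial: "This is an 8-week, open-label, phase 1 clinical trial assessing the safety, tolerability, and efficacy of MET-2".
- **Secondary Objectives** lists safety and tolerability, and also the aim to "assess changes in metabolic functioning/levels before, during, and after treatment", without naming analytes.
- **Safety and Tolerability** judges product safety from recorded symptoms and adverse events, and tolerability also from two rating scales.

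**The concern.** The product contains 40 live bacterial strains and, by the article's own account, has not been tested before in psychiatric indications. A shift in blood count, creatinine or electrolytes need not produce a symptom. If it does not, a safety assessment built on symptoms and adverse events will not show it unless someone happens to order the test. A later statement that no safety signal was seen would then have no planned data behind it for these analytes.

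The usual reply, that a journal article leaves detail to the full protocol, does not work here. The article states that the panel is taken at screening alone, so it sets a rule and does not leave a gap. The omission also saves little, because blood is taken twice more in any case.

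Glucose adds a smaller point. It is a natural candidate for the metabolic objective, but with one pre-treatment value it cannot contribute to it.

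**Working it through.** The plan gives no figure to reproduce, and no power or alpha calculation is involved. The check is a count of scheduled values per participant.

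**Inputs.** Draw times come from Molecular Analysis and Table 2 (screening, week 4, week 8). Analyte assignment comes from Molecular Analysis. The planned sample size of 10 to 15 comes from Participants. The achieved numbers come from Results: 21 enrolled, 12 of whom completed with at least one post-baseline visit.

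**Step 1: scheduled values.**

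| Analytes | Before treatment | Weeks 4 and 8 |
|---|---|---|
| Complete blood count, creatinine, electrolytes, glucose, TSH | 1 | 0 |
| Cortisol, liver function, lipids, inflammatory markers including C-reactive protein, neurotransmitters, immunoglobulins | 1 | 2 |

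**Step 2: what can be estimated.** Change = on-treatment value − screening value. This needs at least one value of each kind. The second row of the table has both, at two time points. The first row has no on-treatment term, so no scheduled change exists for any participant.

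**Step 3: what the existing draws could supply.** Values per analyte = participants × 2 draws.

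- Planned minimum: 10 × 2 = 20.
- Planned maximum: 15 × 2 = 30.
- Participants reported as completing: 12 × 2 = 24. This is a ceiling that assumes all 12 gave blood at both weeks, which the article does not say.

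**Step 4: the metabolic objective.** The objective names no analyte. The abstract describes its source broadly: "Molecular data will be collected from blood and fecal samples to assess metabolic changes". Lipids, liver function and cortisol are each measured at screening, week 4 and week 8, so the objective has data. A glucose component would be unavailable, but none is promised.

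**Step 5: pregnancy, a separate matter.** Discontinuation Criteria lists new pregnancy as a possible reason to stop treatment. Table 2 schedules a pregnancy test at week 0 and at no later visit. During the 8 treatment weeks the criterion has no scheduled test behind it.

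**The case against.** The strongest case on the other side has five parts.

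1. **The choice is deliberate.** The panel has a stated purpose, and no section promises on-treatment haematology or renal results. This stands: the schedule does not contradict anything else in the article. It does not show that the schedule suits the stated safety aim.
2. **Laboratory follow-up exists.** Liver function, lipids, C-reactive protein, cytokines and immunoglobulins are all repeated. The investigator can record clinically relevant abnormalities as adverse events, and the serious adverse event form asks for laboratory findings. This also stands. A reader might infer that the trial could not detect any change in the screening-only analytes, and the article does not support that. What is missing is a *scheduled* value. Event-driven tests still cannot fill that gap, because they are done in selected participants at unplanned times.
3. **Glucose is not an endpoint.** A reader might infer that the metabolic objective fails without it. It does not, because the objective names no analytes and has other repeated measures.
4. **Translocation is covered.** The Introduction mentions "bacterial translocation from the gut", and a reader might take this as a product risk left unmonitored. The text is background on the causes of depression. The IgA and IgM response it describes is measured again at weeks 4 and 8, together with C-reactive protein and cytokines. The passage therefore lends the point no weight.
5. **It is too late.** Recruitment ended in December 2019, and nothing says that suitable blood was kept. For this trial that limits the remedy to reporting. It does not make the schedule sound.

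**Conclusion.** The point holds as a design weakness of moderate weight that should be corrected. Neither of the two on-treatment draws carries blood count, creatinine, electrolytes, glucose or TSH, so the plan yields no scheduled within-person change for them. Safety is a secondary objective, and the primary objective concerns mood and anxiety. The weakness therefore narrows what can be said about safety and leaves the efficacy analysis untouched.

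The conclusion assumes that Molecular Analysis reports the full protocol's schedule accurately. The count of 20 to 30 recoverable values assumes that every planned participant attends both draws.

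The mismatch between the pregnancy criterion and the test schedule is a separate, smaller matter. The article does not show which of the two was intended.

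**What to change.** **Schedule.** In Molecular Analysis, remove the restriction to screening for complete blood count, creatinine, electrolytes and glucose, and state that they are also run on the blood drawn at weeks 4 and 8. TSH may stay at screening if the protocol says so as a choice.

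**Reporting.** For these four, present change from screening and shifts outside the laboratory reference range, alongside the liver function results. Glucose could then also inform the metabolic objective, provided the objective lists its analytes.

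**Cost.** Routine assays, slightly more blood per draw, and some chance abnormal values that someone must review. No further visit or venepuncture is needed, because the draws are already in Table 2.

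**If the draws are already complete.** State in the report that haematology, renal function, electrolytes, glucose and TSH were not scheduled on treatment, and that the safety conclusion does not extend to them. This costs one sentence.

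**Separately.** Reconcile the new-pregnancy entry in Discontinuation Criteria with the week 0 pregnancy test in Table 2, so that the article says how the criterion is meant to be ascertained.
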